## Abstract

**Background:**

Accessing opioid use disorder (OUD) treatment is difficult for individuals with unstable housing. This population often uses public libraries for computer and internet access, which could provide telehealth access to OUD treatment. Therefore, we developed a novel 12-week library-facilitated telehealth intervention study called “Bupe by the Book” (BBB) that uses library resources to facilitate initiation and retention in OUD treatment with buprenorphine.

**Methods:**

The study is a partnership between the San Diego Public Library and a federally qualified healthcare center attached to a homeless shelter (Father Joe’s Villages (FJV) Village Health Center). We co-designed a pilot randomized controlled trial to assess the feasibility and acceptability of a library-facilitated telehealth intervention in San Diego, California. The intervention is being evaluated for its feasibility and acceptability (library tele-buprenorphine uptake) by obtaining an estimate of the effect of the library telehealth arm of the intervention on buprenorphine treatment outcomes (primary outcome: buprenorphine uptake, i.e., a pharmacy pickup and taking the prescription 1 + times) and adherence (i.e., > 1 buprenorphine positive screens, ideally for 8 + weeks), compared to the control (standard care at the clinic) intervention. Individuals reporting homelessness and OUD (with or without other substance use) are eligible. Forty library patrons will be recruited via flyers, screened for eligibility, and referred to FJV Health Center for in-person initial buprenorphine treatment intake visits. Participants who complete intake are enrolled and randomized to the library-facilitated telehealth condition, which involves using library internet and computer resources for follow-up buprenorphine treatment appointments with the medical provider via library telehealth. In the control condition, participants do not use library telehealth for their buprenorphine care follow up appointments, but rather they go in-person to the clinic or per usual standard care protocols. Feasibility and acceptability of the library telehealth intervention and conduct of the randomized controlled trial are determined by the participants’ use of the library telehealth intervention for buprenorphine treatment, and quantitative and qualitative measures assessing their perceptions of the library telehealth intervention, collected over a 12-week period.

**Discussion:**

The design of this pilot study may support the adoption of library-facilitated telehealth treatment as a feasible and acceptable strategy to engage and retain people experiencing homelessness with OUD in buprenorphine treatment.

**Trial registration:**

This trial was registered prospectively at ClinicalTrials.gov (registration number NCT05872386) on May 24, 2023.

## Background

Recently, overdose deaths in the U.S. have increased by as much as 30% compared to prior years [1]. In San Diego County, California, 814 fentanyl-related deaths occurred in 2022 compared to 462 in 2020 [2]. In the fight to treat opioid use disorder (OUD), efforts to integrate buprenorphine into primary care and other settings has been ongoing for over twenty years as a promising medication that can be prescribed or dispensed by physicians in medical offices [3].

In the U.S., over half a million people experience homelessness [4]. The city of San Diego, California, has the fifth largest unhoused population nationally [5] and a rapidly increasing population with OUD [6]. Nearly 30% of unstably housed persons struggle with mental health and substance use disorders [7]. Many persons with OUD remain houseless and profoundly hard to reach.

Buprenorphine is a highly effective treatment for OUD that has been shown to reduce the risk of opioid overdose [8]. In 2023, overdose deaths decreased nationally by 3% for the first time since 2018 [9]. However, formidable barriers to buprenorphine uptake remain challenging, especially for uptake among persons who are experiencing homelessness [10], accounting for 38.7% of reported overdose deaths across San Diego County in 2022 [2, 11, 12].

Overdose deaths among unhoused individuals in San Diego increased 233% from 2019 to 2023 [2]. Unhoused people are disproportionately impacted by the overdose crisis. Buprenorphine uptake (i.e., a pharmacy pickup and taking the prescription one or more times) and adherence (i.e., more than one buprenorphine positive screen, ideally 8 + weeks) may depend on an individual’s housing status and other issues impacting their ability to participate in treatment.

Typically, patients follow an individualized plan that includes visits for medication management, counseling sessions, and urine drug screenings. However, our preliminary work showed that unstably housed persons with OUD at libraries report barriers to following this plan, including a lack of transportation for in-person visits, a lack of smartphones or computers for telehealth encounters, and a lack of consistent telephone numbers/devices for telephone visits [13, 14].

Other barriers to uptake and adherence, such as stigma, lack of knowledge of medications, high out-of-pocket costs, inconsistent insurance coverage, and ethnic disparities related to medication access, are well-documented [15–23].

Additionally, studies show disadvantages for those with digital literacy barriers [24]. Unhoused individuals are less likely to have reliable interconnectivity [25]. As such, public libraries present themselves as public health opportunities to facilitate telemedicine [25] by providing computers, high-quality internet connection, and private spaces where patrons can conduct confidential telehealth calls. Therefore, one place to find unstably housed persons is the public library.

Nationwide, public libraries face an on-site opioid overdose crisis [27, 28], especially among its unhoused patrons. A randomized survey of five U.S. states showed that 12% reported at least one on-site overdose in the prior year [27]. In another study of Ohio’s 251 public library systems, over 60% of 56 survey respondents indicated awareness of on-site opioid-related incidents (transactions, consumption, or overdose) [28]. Data from our own formative research, according to unstably housed individuals in focus groups in downtown San Diego, revealed as much as “two overdoses a day” occurred just outside the library among those experiencing homelessness and other harms [13, 14, 29–32]. Libraries offer a safe place for many unhoused individuals during the day, and numerous libraries have already taken extraordinary measures to help those with OUD [8, 33]. Some libraries now have on-site social workers, nurses, and peer homeless outreach staff [13, 33–45]. In the downtown San Diego Central Library, library security staff are trained to carry and administer Naloxone to patrons who overdose in the bathrooms and around the immediate vicinity. Because individuals experiencing homelessness and OUD regularly patronize public libraries, a public health opportunity presents itself to offer OUD treatment.

Telehealth interventions for buprenorphine, delivered per national standards, provide patients with buprenorphine prescription access through remote telehealth (audio and video or even audio only) sessions with a prescribing medical provider without having to go to in-person clinic visits as frequently or ever. Research shows that telehealth interventions for buprenorphine effectively overcome barriers to buprenorphine uptake/adherence [10]. After the U.S. Drug Enforcement Administration relaxed requirements for prescribing buprenorphine in March 2020 (during the COVID-19 pandemic), studies began highlighting low-barrier buprenorphine treatment options as more accessible under the national regulatory changes [46–48]. The studies include unhoused persons in San Francisco [49], mobile buprenorphine/case management for homeless veterans [50], and a van-based buprenorphine induction clinic in partnership with a federally qualified health center [51]. A review of telehealth-delivered medications for OUD found that a videoconference intervention led to better substance use treatment retention than an in-person group [47, 48, 51–53]. These studies suggest that telehealth can promote the initiation of buprenorphine.

This protocol describes our “Bupe by the Book” (BBB) study, conducted in collaboration with established local partners, including San Diego Public Libraries and Father Joe’s Villages - Village Health Center (FJV), a federally qualified healthcare center (FQHC). Previously, FJV provided patients with an option for tele-buprenorphine (telehealth for buprenorphine) for those who reported access to a device (e.g., computers, smartphones, tablets, or telephones).

Representing a significant step further, the Bupe by the Book study removes the need for access to a device. Instead, it leverages public library resources (devices and internet) to allow individuals experiencing homelessness to access telehealth care for buprenorphine. BBB is a groundbreaking intervention evaluated using a 12-week, two-arm randomized controlled trial (RCT) design. By testing library-facilitated telehealth, the study informs how unstably housed persons and others can potentially receive buprenorphine care innovatively with minimal clinical/non-clinical requirements (e.g., low-barrier induction offered without a waiting period). 

## Methods

### Objectives and hypotheses

The overall objective of this study is to determine the feasibility and acceptability of utilizing library-facilitated telehealth to provide buprenorphine access to unstably housed people with OUD. Feasibility metrics include recording the number of telehealth visits in the library (with buprenorphine providers) and the proportion of patrons, library, and health providers who say they have preference or feel neutral about library telehealth vs. opposition to it. Acceptability includes interviewing participants throughout and at the end of the study, as well as health providers and library staff, about their acceptability and appropriateness of using library tele-buprenorphine.

Feasibility and acceptability of the library telehealth intervention and conduct of the randomized controlled trial will also be determined by the participants’ use of the library telehealth intervention for buprenorphine treatment, and quantitative and qualitative measures assessing the acceptance of the library telehealth intervention, collected over a 12-week period and at exit. As a benchmark, we anticipate that most participants will be retained in the study and will use the library telehealth intervention as assigned. The libraries and the clinic will also be willing and able to implement the telehealth intervention. Specifically, we will measure feasibility and acceptability in the following ways:

#### Feasibility of the telehealth intervention

Proportion of telehealth intervention arm participants who complete at least one telehealth visit appointment at the library.Proportion of scheduled visits with the buprenorphine provider that participants attend via telehealth at the library.We will also document any barriers to telehealth that arise (e.g., internet connection issues).

#### Acceptability of the telehealth intervention

Qualitative interviews are conducted during the intervention and via exit interviews asking about the participants’ experiences with telehealth, as well as the library and clinic staff’s experiences with delivering the library telehealth.Survey measures also measure the participants’ experiences with telehealth in general to see if changes occur over the course of the study.

#### Feasibility of RCT to evaluate the current intervention

Rate of enrollment (Number of participants per week and per month).Proportion of interested and eligible participants who can successfully complete enrollment in the study.Study retention (proportion of RCT-enrolled participants who complete each follow-up assessment).Proportion of RCT-enrolled participants for whom outcome data are collected.We will track the proportion of participants who indicate willingness to be assigned to either condition (the percent of people who decline to participate because they do not like the randomization aspect of the study should be “none” to determine whether the study is feasible).

As a pilot study that is not statistically powered to assess efficacy, the study will provide effect size estimates of the library-facilitated telehealth BBB intervention on the primary outcomes, buprenorphine uptake and adherence, as measured by (1) presence of buprenorphine in weekly urine drug screenings at the library and at FJV health center, (2) buprenorphine prescription pick-ups, and (3) number and frequency of clinic visits, with secondary outcomes including use of fentanyl (e.g., illicitly manufactured) and other opioids (secondary outcome measured in weekly urine drug screens), and (4) self-reported substance use, mental health, and quality of life measures at 1-,2-,4-,8-, and 12-weeks, compared to a control group.

The control group will undergo the same procedures and receive the same incentives from the study staff in the library in terms of weekly assessments. They will also receive the same care from the clinic, except they will not be instructed to use the library telehealth option for their medical visits like the treatment group until their study participation is over. We hypothesize that patrons assigned to the library-facilitated telehealth group will uptake buprenorphine, pick up their buprenorphine prescriptions from the pharmacies, take buprenorphine after two weeks, and adhere to medical appointments more than the control (in-person clinic visits) group.

As a primary outcome, buprenorphine *uptake* is defined as a pharmacy pickup and taking the prescription one or more times during the study period. Buprenorphine *adherence* is indicated by more than one buprenorphine positive screens taken at the library or at FJV Health Center and ideally continuing to take buprenorphine as prescribed for eight or more weeks. The rationale for the primary outcomes, buprenorphine uptake and adherence, via weekly drug screening, is to try to capture the patterns of buprenorphine uptake and adherence among unhoused populations, a likely more isolated and neglected group when it comes to finding, starting, and adhering to buprenorphine due to being unhoused. Therefore, we measure adherence as a primary outcome with 1 + buprenorphine positive tests, ideally for 8 + weeks of 12 weeks (3 months), rather than the standard 3–12 months adherence.

In the study’s formative stages of intervention development, study staff conducted interviews and focus groups with library patrons (those experiencing homelessness or living in a shelter or treatment program), library staff (i.e., security personnel, librarians, outreach workers), general public/parents, and buprenorphine providers to get reactions to the proposed program and to inform the study design. For example, five focus groups with library patrons were conducted across four libraries in San Diego to assess the potential feasibility and acceptability of the planned intervention. The findings from these interviews and focus groups inform the design of the telehealth intervention at the libraries and the measures that can be used in a randomized controlled trial. For example, we gained insights for recruiting and screening participants for opioids (being discreet in public spaces), enrollment procedures (coordinating with medical providers), and timing of the randomization (after first buprenorphine medical provider visit). Another recommendation made is to have persons with lived experience, especially with substance use recovery and experiences with buprenorphine, on the team. Focus group participants suggested recruitment strategies such as placing flyers at specific library bulletin boards frequently visited by unhoused individuals, which many identify as providing a consistent and reliable source of community information.

Many participants feel that using the library setting for care can facilitate an added layer of discreteness for their clinical care by providing a setting to receive medication for opioid use disorder without fear of going to a clinic. Going in-person to a clinic could result in stigma from being identified as someone receiving substance disorder treatment. Further, several participants view the library as a safe location associated with reduced opportunities for encountering environmental triggers for use that may be present in a clinical setting (e.g. large waiting rooms with other individuals who also use drugs or have other mental health issues, pressure to use drugs from people congregating outside clinics for other services). The participants suggest ways to further keep participation in the study confidential at the library by using telehealth services and conducting study visits in private study rooms.

The focus groups and interviews with medical service providers and library staff helps determine ways to keep the study procedures in line with the usual clinic and library protocols to minimize the need for additional costs and staff time at either place, as well as design a protocol with a great likelihood for implementation after the study. For example, process measures are determined to be conducted by the research staff at intervals commensurate with clinical care for buprenorphine (e.g. in-between and at 1-,2-,4-,8-,12- weeks). The timeframe for determination of buprenorphine uptake outcome measures and follow-up visit schedules are vetted with the medical staff commensurate with the standard of care. The formative data gathering helps inform how we collect our process measures (e.g., meeting regularly with the health center to gather appointment keeping data). The clinic and researchers should conduct regular meetings during the duration of the study to ensure a functional and efficient trial.

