#### Sample size and planned data analyses

Our target sample size for the trial is 40 participants, although we allow for a maximum of 60 participants to account for attrition. The sample size will provide adequate precision for effect size estimates, though not statistically powered to assess efficacy on primary outcomes.

Buprenorphine uptake (the proportion who pick up and take buprenorphine at initiation, confirmed by CURES database pharmacy pickup records and urinary drug screenings) and adherence (taking buprenorphine > 1 time, ideally for 8 + weeks), medical appointment adherence (attended medical appointments for buprenorphine two or more times as confirmed by clinic medical record data) will be divided by the number prescribed and scheduled, respectively.

Adherence estimates from this study will also provide the basis for power calculations in the design of future efficacy trials. Quantitative data analysis will consist of univariate statistics to describe the entire study sample and by study arm, the prevalence of individual responses, and the prevalence of treatment uptake and adherence. We will conduct an intent-to-treat (i.e., per-randomization) analysis following CONSORT guidelines to explore potential differences between study arms on the outcomes. Specifically, we will use regression models testing each outcome separately (using the appropriate test depending on the outcome distribution, e.g., logistic regression with binary outcomes). These models will treat the intervention condition (library-facilitated telehealth intervention vs. treatment-as-usual control) as the exposure in unadjusted models.

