#### Timeline and dissemination plans

Results from the BBB study will be disseminated widely to organizational, clinic, and library partners, community networks, and nationally at substance use and library information science conferences in consultation with our community partners. Summary findings for community members (non-scientists) will be written following best practices for providing medical information to the public [61]. We will share results with our research partners and stakeholders (e.g., County) via open-access peer-reviewed publications, reports, news media outlets, and conference and community presentations. We aim to eliminate barriers to future Phase III efficacy trials by including residents, patients, providers, and libraries’ input before the study’s pilot. We intend to disseminate this information to these groups through such outlets.

Effect size estimates may also inform subsequent intervention research, including a fully powered efficacy trial, with this population and setting (see Fig. 1).

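### The feasibility criterion of zero refusals because of randomisation would often be failed by a well-accepted design; it should be a proportion judged against a tolerable maximum

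*Protocol article*

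**What the plan says.** The protocol article makes feasibility and acceptability the overall objective (Objectives and hypotheses). The section Feasibility of RCT to evaluate the current intervention lists five measures. Four carry no cut-off: rate of enrolment, completion of enrolment, retention at each follow-up, and availability of outcome data. The fifth is willingness to be assigned to either condition. It alone has a definite value, *none*, which the article attaches to this quantity: "the percent of people who decline to participate because they do not like the randomization aspect of the study should be". The same sentence presents that value as the means of deciding on feasibility.

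Objectives and hypotheses adds two unquantified statements: "As a benchmark, we anticipate that most participants will be retained in the study and will use the library telehealth intervention as assigned" and "The libraries and the clinic will also be willing and able to implement the telehealth intervention". Table 2 repeats the feasibility measures without cut-offs. Nothing elsewhere in the article softens the word *none*.

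On size, Sample size and planned data analyses says: "Our target sample size for the trial is 40 participants, although we allow for a maximum of 60 participants to account for attrition". These are numbers enrolled. The article does not say how many eligible people are expected to be told about randomisation and asked to take part.

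**The concern.** A zero-event criterion becomes harder to meet with every additional person asked, however acceptable the design is. A refusal rate of 1% or 2% would not by itself threaten a larger trial, yet one refusal is enough to miss *none*. The criterion also gives no measure of how far short the design fell, because one refusal and ten refusals both simply fail.

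The pilot is meant to lead on to further work: "Effect size estimates may also inform subsequent intervention research, including a fully powered efficacy trial, with this population and setting". Whether people accept randomisation is one of the main things such a pilot can teach. If the stated criterion is likely to be missed for a trivial reason, the investigators must either report a misleading negative on this measure or reinterpret the criterion after seeing the data. Neither is desirable for a primary question of the pilot.

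**Working it through.** **Inputs**

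- Criterion: 0 refusals because of randomisation (Feasibility of RCT to evaluate the current intervention).
- Number asked, *n*: not given. I assume 40 and 60, the target and maximum enrolment, and also show 80. If the target of 40 is reached, at least 40 people must have been asked. Screening and enrollment expects some people to start enrolment and not finish, so the number asked is likely to be larger.
- True share refusing because of randomisation, *p*: not given. I assume 0.5% to 10%.
- Decisions are taken as independent between people.

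The article gives no calculation behind *none*, so there is no stated figure to reproduce.

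**1. How often the criterion fails**

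P(at least one refusal) = 1 − (1 − p)^n. For example, at p = 2% and n = 40: 1 − 0.98^40 = 1 − 0.446 = 0.554.

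| True refusal rate | n = 40 | n = 60 | n = 80 |
|---|---|---|---|
| 0.5% | 18% | 26% | 33% |
| 1% | 33% | 45% | 55% |
| 2% | 55% | 70% | 80% |
| 5% | 87% | 95% | 98% |
| 10% | 98.5% | 99.8% | >99.9% |

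**2. What true rate would give a good chance of passing**

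For an 80% chance of no refusals, p = 1 − 0.8^(1/n). This gives 0.56% at n = 40 and 0.37% at n = 60. Only near-universal acceptance passes reliably.

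**3. What a pass would show**

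With 0 of n refusing, the one-sided 95% upper bound is 1 − 0.05^(1/n), which is 7.2% at n = 40 and 4.9% at n = 60. The two-sided (Clopper-Pearson) upper limit is 1 − 0.025^(1/n), which is 8.8% and 6.0%.

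Compare a bare fail. One refusal in 40 is 2.5%, with a Clopper-Pearson 95% interval of 0.1% to 13.2%. That overlaps heavily with the 0% to 8.8% from 0 of 40, yet the two results fall on opposite sides of the criterion.

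**4. How a tolerable maximum would behave**

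For illustration only, take at most 10% declining, which is at most 4 of 40 or 6 of 60. P(pass) is the binomial probability of that many refusals or fewer.

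| True refusal rate | ≤4 of 40 | ≤6 of 60 | None of 40 |
|---|---|---|---|
| 2% | 99.9% | >99.9% | 45% |
| 5% | 95% | 97% | 13% |
| 10% | 63% | 61% | 1.5% |
| 20% | 8% | 3% | <0.1% |

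The illustrative rule usually passes low refusal rates and usually fails high ones. The zero rule also fails the high rates, but it fails most of the low ones with them.

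**The case against.** The strongest reply is that *none* sits in a parenthesis, is introduced by *should be*, and belongs to one of five trial-feasibility measures. These stand beside telehealth use, visit attendance, documented barriers, surveys and interviews. The article states no progression rule and attaches no stopping consequence to any measure. This stands, and it limits the point. A reader might infer that one refusal would have the whole study declared infeasible or block a later trial, but the documents do not say so. It does not remove the point, because the sentence says the value is there to determine whether the study is feasible, and nothing else relaxes it.

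A second reply is that the refusal rates and the number asked are not in the documents. That is correct, which is why a range is shown. At a true 0.5% with 40 asked, the criterion would still be met 82% of the time (1 − 0.18). The conclusion weakens only at rates well under 1%.

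Two stronger readings are tempting and not supported:

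- A reader might infer that the benchmark of *most* participants being retained and using library telehealth is a second faulty threshold, met by a bare majority such as 11 of 20. The article words it as an anticipation and gives no pass mark, and the bare-majority reading and a 1:1 split would both be the reader's own. Leaving it unquantified is detail that an article may leave to the full protocol.
- A reader might infer that measuring willingness among *participants* yields 100% by construction, because people who decline are not participants. The same sentence counts people who decline, and the same section uses *participants* for people who have not yet completed enrolment. The denominator would be clearer if stated, but the text does not fix it at the enrolled.

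**Conclusion.** The point holds for the zero-refusal criterion alone. Taken as written, with 40 to 60 people asked, it would be missed with probability 33% to 45% at a true refusal rate of 1%, 55% to 70% at 2% and 87% to 95% at 5%. A miss therefore says little about whether randomisation is well or poorly accepted, and meeting it with 40 asked leaves true rates up to about 7% to 9% open. These figures rest on assumed refusal rates, an assumed number asked and independence between people. If more than 60 are asked, the criterion is missed more often.

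The consequence is a badly set criterion for one feasibility measure. It is not a fault in the trial's overall feasibility judgement, which the article bases on several measures together.

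**What to change.** In Feasibility of RCT to evaluate the current intervention, replace *none* with a proportion:

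- numerator: eligible people who decline because of randomisation;
- denominator: all eligible people told about randomisation;
- reporting: the estimate with its 95% confidence interval;
- judgement: against a tolerable maximum that the sponsor chooses and states before the results are seen. The 10% used above is only an illustration.

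Record the reason for declining alongside the count, already planned in Screening and enrollment, of people who start enrolment but do not complete it at the clinic. Make sure that people who decline before starting enrolment are entered too, since a refusal because of randomisation may come at that stage.

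The cost is a change of wording and one added field. The sample size and the trial procedures do not change.
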